# Study protocol: a single-blind, multi-center, randomized controlled trial comparing dynamic intraligamentary stabilization, internal brace ligament augmentation and reconstruction in individuals with an acute anterior cruciate ligament rupture: LIBRƎ study

**DOI:** 10.1186/s12891-019-2926-0

**Published:** 2019-11-18

**Keywords:** Orthopaedics, Knee, Anterior cruciate ligament, Acute anterior cruciate ligament rupture, Anterior cruciate ligament reconstruction, Anterior cruciate ligament repair, Anterior cruciate ligament injury

## Abstract

**Background:**

The current gold standard for the treatment of an anterior cruciate ligament (ACL) rupture is reconstruction with tendon graft. Recently, two surgical ACL repair techniques have been developed for treating an acute ACL rupture: Dynamic Intraligamentary Stabilization (DIS, Ligamys®) and Internal Brace Ligament Augmentation (IBLA, *Internal*Brace™). We will conduct a single-blind, multi-center, randomized controlled trial which compares DIS, IBLA and reconstruction for relative clinical efficacy and economic benefit.

**Methods:**

Subjects, aged 18–50 years, with a proximal, primary and repairable ACL rupture will be included. DIS is preferably performed within 4 weeks post-rupture, IBLA within 12 weeks and reconstruction after 4 weeks post-rupture. Patients are included in study 1 if they present within 0–4 weeks post-rupture and surgery is feasible within 4 weeks post-rupture. Patients of study 1 will be randomized to either DIS or IBLA. Patients are included in study 2 if they present after 4 weeks post-rupture and surgery is feasible between 5 and 12 weeks post-rupture. Patients of study 2 will be randomized to either IBLA or reconstruction. A total of 96 patients will be included, with 48 patients per study and 24 patients per study arm. Patients will be followed-up for 2 years. The primary outcome is change from baseline (pre-rupture) in International Knee Documentation Committee score to 6 months post-operatively. The main secondary outcomes are the EQ-5D-5 L, Tegner score, Lysholm score, Lachman test, isokinetic and proprioceptive measurements, magnetic resonance imaging outcome, return to work and sports, and re-rupture/failure rates. The statistical analysis will be based on the intention-to-treat principle. The economic impact of the surgery techniques will be evaluated by the cost-utility analysis. The LIBRƎ study is to be conducted between 2018 and 2022.

**Discussion:**

This LIBRƎ study protocol is the first study to compare DIS, IBLA and ACL reconstruction for relative clinical efficacy and economic benefit. The outcomes of this study will provide data which could aid orthopaedic surgeons to choose between the different treatment options for the surgical treatment of an acute ACL rupture.

**Trial registration:**

This study is registered at ClinicalTrials.gov; NCT03441295. Date registered 13.02.2018.

## Background

The anterior cruciate ligament (ACL) is an important stabilizer of the knee. The ACL prevents anterior tibial translation and provides constraint to tibial internal rotation [1]. 2.5% of the ACL consists of proprioceptors [2, 3], which give feedback to the brain and spinal cord about the positioning of the knee joint. These proprioceptors play a role in defining and controlling normal joint movement [4]. Abnormal range or speed movements of the joint will trigger the brain to stimulate appropriate musculature to stabilize the joint.

Injury to the ACL is the most common ligament injury of the knee joint. Ruptures of the ACL mainly occur in young people (aged 16–40 years) performing pivoting sports like football, hockey, basketball and skiing. Each year 0.03 to 1.62% of amateur athletes and 0.15 to 3.67% of professional athletes are affected [5]. In Belgium, 6.745 cruciate ligament surgeries were performed in 2017 (according to RIZIV/INAMI, Belgian National Sickness and Invalidity Insurance Institute). The socio-economic burden is considerable as the majority of ACL injuries occur in people of working age. The indirect costs related to absence from work, school or university are in addition to costs borne by the healthcare system [6].

Since the mid-eighties the gold standard for an operative treatment of an ACL rupture is reconstruction with a tendon graft. This involves removing native ACL tissue including its proprioceptors. The ligament is often replaced with autograft donor tendon(s), such as a hamstrings tendon or a part of the patellar tendon. A number of problems have been identified as graft harvest is associated with a degree of morbidity from tissue loss. Hamstrings muscle weakness following harvesting averages 10% in most studies [7]. Revascularization of the graft takes 6–12 months and ingrowth of the graft in the bone takes up to 2 years [8]. Another disadvantage of conventional ACL reconstruction is the rather long period of revalidation associated with a huge socio-economic burden. A successful recovery from an ACL reconstruction encompasses intensive physiotherapy and requires a lot of effort, dedication, time and perseverance. According to Ardern et al. [9], the return to competitive sports after ACL reconstruction is only 44 to 55%. In another study, Biau et al. [10] found that only 40% of patients gain full functional recovery. Nagelli and Hewett postulated that delay in returning to sports for the first 2 years will significantly reduce the incidence of second ACL injuries [11]. Given the limitations and risks associated with the current gold standard treatment of an ACL rupture, there is room for improvement.

The last few years there is a renewed interest in ACL repair as an alternative operative treatment for the acute ruptured ACL. Two novel surgical ACL repair techniques have been developed and proof of concept has been established for treating an acute ACL rupture: Dynamic Intraligamentary Stabilization (DIS, Ligamys®, Mathys Ltd., Bettlach, Switzerland) and Internal Brace Ligament Augmentation (IBLA, *Internal*Brace™, Arthrex GmbH, Naples, Florida) repair techniques [12, 13].

The DIS technique has been shown to successfully induce self-healing of a ruptured ACL in animal models. Biomechanical studies in human cadaveric knees have shown that DIS restores knee joint kinematics comparable to that of an ACL-intact knee and provide further evidence that DIS is capable of providing knee joint stability during ACL healing [14–16]. A clinical experience of the first 3 years after DIS in a large case series was reported by Henle et al. [17]. They found that anatomical repositioning, along with DIS and micro-fracturing, leads to clinically stable healing of the ruptured ACL in 96% of patients. In their study, most patients exhibited a normal knee function, reported excellent satisfaction, and were able to return to their previous levels of sports activities. The same group also presented excellent outcomes and satisfaction with regards to the treatment result of all the patients with a functionally healed ACL with a 5-year follow-up [18]. Factors influencing the success of ACL repair with DIS were described by Krismer et al. and focus on patient selection [19]. In general, a higher percentage of successful outcomes after ACL repair are seen in patients with an acute, proximal ACL rupture because these tend to have better healing capacity and tissue quality. Although no significant differences were found in treatment costs and revision rates, patients treated by DIS benefited from nearly 1 month shorter absence from work as compared to patients treated by conventional ACL reconstruction. This was possibly due to the fact that the DIS procedure is recommended up to the first 21 days after ACL injury. For an ACL reconstruction there is no time limit [20].

Relatively little data is available in the literature on the IBLA technique. The proof of concept was provided by Mackay et al. [21]. They reported clinical outcomes at a minimum of 1 year follow-up, and found that IBLA is at least as effective in restoring stability and function of the knee as the conventional ACL reconstruction, with the greatest improvements seen in the decreased time of recovery. The same group also presented good functional outcomes along with radiographic and arthroscopic evidence of a healed ACL, in one of the first patients treated with IBLA [22]. In a 2 year follow-up of 42 patients treated with the IBLA technique, two patients (4.8%) reported an ACL re-rupture. Heusdens et al. conclude that repair with this technique could be clinically relevant as a treatment option for patients with an acute, proximal ACL rupture which is not retracted and of good tissue quality [23]. In addition, Smith et al. demonstrated the potential for excellent outcomes for paediatric ACL repair with temporary IBLA as an attractive alternative to ACL reconstruction [24].

To our knowledge, there is only one randomized controlled trial (RCT) published comparing an ACL repair technique with the conventional ACL reconstruction [25]. Hoogeslag et al. concluded that DIS is not inferior to ACL reconstruction in terms of subjective patient-reported outcomes 2 years postoperatively, but for reasons other than revision ACL surgery due to re-rupture a higher number of related adverse events were seen in the DIS group [25].

Furthermore, there are no RCTs published comparing different ACL repair techniques with each other. Because of the lack of RCTs orthopaedic surgeons are careful in adapting these new repair techniques. This clinical trial was designed in order to provide more scientific evidence on which of the three surgery techniques could possibly be the most clinically and economically effective for treating an acute ACL rupture.

## Methods

### Study objectives

#### Primary objective

To determine the clinical efficacy of two alternative techniques DIS and IBLA in comparison to the conventional ACL reconstruction for treating an acute ACL rupture.

We are interested in the three pairwise comparisons between the techniques: DIS versus ACL reconstruction, IBLA versus ACL reconstruction and DIS versus IBLA.

#### Secondary objectives

To assess whether DIS and IBLA offer an improvement in quality of life, patient satisfaction and functioning of the patient compared to conventional ACL reconstruction.To assess whether DIS and IBLA result in a shorter recovery period compared to conventional ACL reconstruction in terms of the mobilization period with crutches after the surgery, and return to work and sports period.To assess whether there is a difference between DIS and IBLA versus conventional ACL reconstruction in terms of pain and complications during and after surgery.To assess whether there is a difference between DIS and IBLA versus conventional ACL reconstruction in terms of ACL re-ruptures/failures.To determine the economic benefit of the two alternative techniques DIS and IBLA in comparison to the conventional ACL reconstruction for treating an acute ACL rupture.For all of these objectives also the mutual comparison between DIS and IBLA will be considered.

### Study design

The **LIBRƎ** trial is a single-blind, multi-center, prospective, RCT comparing **L**igamys® anterior cruciate ligament (ACL) repair, ***I****nternal***B**race™ ACL repair and conventional ACL **re**construction for relative clinical efficacy and economic benefit.

Patients admitted for an acute traumatic knee sprain needing ACL surgery will be recruited at the Antwerp University Hospital and University Hospital Brussels, Belgium between February 2018 and June 2020.

The LIBRƎ study is single-blind, meaning that the patient and the physiotherapist are blinded to the performed surgical technique, but they are aware in which part of the study the patient participates (study 1 or study 2). Patient’s physiotherapist will follow a study-specific rehabilitation protocol (identical for the three treatment arms), depending on the readiness of the patient for a next phase and not restricted to a predefined time line.

In the study design, the time-dependent nature of ACL repair surgeries has been taken into account. The company Mathys Ltd. advices DIS to be performed within 3 weeks after the ACL rupture. Previous ACL repair surgery experience from the authors ([name]) led to a prolonged DIS ACL repair period within 4 weeks post-rupture. IBLA can be performed up to 12 weeks after the ACL rupture. ACL reconstruction is preferably performed when the knee has regained its function. This is commonly after 4 weeks post-rupture and can be performed up to many years later. Taken into account these time limits there will be two parallel studies (flowchart, Fig. 1):
Study 1 (RCT 1) with a time frame 0–4 weeks post-rupture: patients are randomized 1:1 to DIS or IBLAStudy 2 (RCT 2) with a time frame 5–12 weeks post-rupture: patients are randomized 1:1 to IBLA or conventional ACL reconstruction.

**Fig. 1 Fig1:**
[figure not shown]
Study flow diagram: screening, inclusion, surgery and follow-up. *Depends on when the patient presents at the consultation desk after the ACL rupture. **Patients in the exploratory group will be replaced, but are still part of the study. ACL = Anterior Cruciate Ligament, DIS = Dynamic Intraligamentary Stabilization, IBLA = Internal Brace Ligament Augmentation, MRI = Magnetic Resonance Imaging

Allocation to either study 1 or study 2 depends on the patient’s admission time point after ACL injury and if it is practically feasible to perform ACL surgery within 4 weeks. There is a patient and referral delay, a magnetic resonance imaging (MRI) needs to be performed to confirm the ACL rupture and the surgery has to be planned. On the other hand, inclusion and surgery between week 5–12 after injury is expected to be more manageable to plan. There will be an intra-operative confirmation in study 1 and study 2 of the ACL’s eligibility for repair. If the proximal ACL rupture is not suitable for repair, ACL reconstruction will be performed. To keep the three arms (DIS, IBLA and the conventional reconstruction arm) comparable, patients with a non-repairable proximal ACL rupture will be replaced by a new patient even if they were randomized to the conventional ACL reconstruction. These patients will be seen as excluded from the randomized medical device (but not excluded from the study) and will undergo a conventional ACL reconstruction (exploratory group). These patients will be treated as a sub-population and will not be included in the primary analysis.

### Study population

#### Inclusion criteria

Primary acute proximal ACL rupture: 3-digit ACL rupture classification, type A (MRI and intra-operative confirmation) [17] (Fig. 2).Age: 18–50 years.Presented and planned surgery within 4 weeks after the ACL rupture (Study 1).Presented and planned surgery between 5 and 12 weeks after the ACL rupture (Study 2).The ACL remnant is suitable for repair in the three treatment arms: at least 75% of the distal ACL remnant must be in contact with the proximal remnant/femoral condyle (intra-operative confirmation).Mentally and verbally capable of participating in the study.Written informed consent (according to the ICH-GCP Guidelines).

**Fig. 2 Fig2:**
[figure not shown]
Three-digit ACL rupture classification. The first digit describes the ACL rupture location: ‘A’ for proximal third, ‘B’ for central third and ‘C’ for distal third. The second digit is the ACL rupture status: ‘1’ for 1 bundle, ‘2’ for 2 bundles and ‘3’ for multilacerated. The third digit describes the ACL synovial tube: ‘1’ for completely intact, ‘2’ for ≥50% intact and ‘3’ for < 50% intact [17]

#### Exclusion criteria

Posterior cruciate ligament injury and/or posterolateral ligamentous complex grade 3 injury, lateral collateral ligament grade 3 injury or medial collateral ligament grade 3 injury.Osseous fractures or trauma that could impair rehabilitation and/or ACL repair.Neurological disorder or systemic disease.Inflammatory disease, rheumatoid arthritis, spondyloarthropathy or active malignancyNon-sportive: Tegner score of less than 3.Not suited for intervention due to lack of mobility, meaning not achieving 90° of flexion before surgery.

### Study intervention

#### Conventional ACL reconstruction

ACL reconstruction involves replacing the torn ligament with a harvested graft (quadrupled semitendinosus) taken from the patient’s ipsilateral knee (Fig. 3) [26]. This arthroscopic procedure involves harvesting the hamstrings tendon graft, removing the ruptured ACL and drilling tunnels in the femur and tibia to place the graft in the same anatomical position as the native ACL. The graft is fixed on the femur with an adjustable suture button, and on the tibia with a post- and interference screw.

**Fig. 3 Fig3:**
[figure not shown]
ACL reconstruction, left knee, frontal view,©Mathys Ltd. Bettlach. Permission was granted by the company©Mathys Ltd. Bettlach to use this picture in a journal article

#### DIS

The DIS repair technique was described by Eggli et al. (Fig. 4) [12]. The tibial stump of the ACL is reduced to the femoral footprint by transosseous sutures thereby restoring the anatomical position of the ACL [15]. Additional to the technique described by Eggli et al., lasso sutures will be used to reduce the tibial stump, if the stump cannot be reduced with PDS sutures. With this adaption, multi-bundle ruptures can be repaired. The knee is stabilized with a strong polyethylene cord which is passed on the tibial side behind the tibial footprint to prevent damage to the ACL tibial blood and nerve supply. At the femoral side the cord is passed through the anatomical footprint after carrying out micro-fracturing at this site. Using a dynamic spring-screw implant, the cord is brought under tension on the anteromedial aspect of the tibia just above the pes anserinus insertion. The proximal tibia is hereby pulled in a constant posterior drawer position with a force of 50–80 Newton depending on the sex of the patient. It is hypothesized that DIS repair continually stabilizes the knee and therefore can enable mechanically stable ACL healing [12].

**Fig. 4 Fig4:**
[figure not shown]
Ligamys® technique, left knee, frontal view. Picture can be found in the ‘Ligamys® Surgical technique’ brochure,©Mathys Ltd. Bettlach. Permission was granted by the company©Mathys Ltd. Bettlach to use this picture in a journal article

#### IBLA

The IBLA repair technique involves repair of the ACL as well (Fig. 5) [13, 27]. The proximal end of the ACL stump is re-approximated against the medial wall of the lateral femoral condyle or the proximal remnant with a lasso suture. The knee is stabilized with a high strength tape, fixed on the femur with a femoral button, passing besides or through the ACL from the femoral footprint to the tibial footprint and fixed on the tibia with a bone anchor. The *Internal*Brace™ reinforces the ligament as a secondary static stabilizer, encouraging natural healing of the ligament by protecting it during the healing phase and supporting early mobilization.

**Fig. 5 Fig5:**
[figure not shown]
*Internal*Brace™ technique, left knee, frontal view. Picture can be found in the ‘ACL Primary Repair with *Internal*Brace™ Surgical technique’ brochure,©Arthrex GmbH. Permission was granted by the company©Arthrex GmbH to use this picture in a journal article

The three surgical techniques will be performed in Antwerp University Hospital and University Hospital Brussels using similar surgical protocols. No additional anterolateral procedure will be performed. In case of a non-repairable ACL rupture, a conventional ACL reconstruction will be performed. In case of failure/re-rupture of the repaired ACL (DIS/IBLA technique) a conventional ACL reconstruction can be performed. In case of failure/re-rupture of the reconstructed ACL, a revision of the reconstruction can be performed.

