#### Secondary endpoints

Pain experienced by the patients as measured by Visual Analogue Scale (VAS) pain score [30, 31].Overall functioning by the patient, related to the knee, as measured by Tegner and Lysholm score [32].Health-Related Quality of Life (HRQoL) as measured by EQ-5D-5 L [33, 34].Time to recovery as measured by mobilization with crutches, return to work and sports.Patient satisfaction towards the surgery and revalidation level as measured by VAS satisfaction.Mechanic functioning of the knee as measured by Lachman test; single leg hop, triple leg hop, triple crossover hop and drop jump test; proprioceptive measurement; isokinetic measurement; and knee function [35–42].Intra- and post-operative complications: adverse device effects (ADEs) and serious adverse events (SAEs).Success of the operation techniques defined as the number of non-failures.
A failure is defined as:
A re-rupture of the graft or the repaired ACL: clinically and MRI-confirmedInstability complaints: AP translation difference of more than 3 mm (Lachman test) between the injured knee and the contralateral knee, and subjective instability complaints [17].The number of physiotherapy and (extra) orthopaedic surgeon consults.ACL healing will be evaluated with MRI [43].

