MRI is performed on a 3 T system (Magnetom Prisma Tim, Siemens, Erlangen, Germany) for IBLA and ACL reconstruction arms. For patients treated by DIS, a 1.5 T system (Magnetom Aera Tim, Siemens, Erlangen, Germany) with metal artefact reduction sequences will be used. The 4-level Howell classification, originally proposed for grading ACL graft, is adapted for evaluating the repaired ligaments [44]. The morphology and signal intensity of the ACL graft or repair will be subjectively assessed on conventional MRI [45].

When re-surgery is needed or a failure occurs, the patient is not excluded from the study and the follow-up will continue according to this protocol. Under re-surgery, we consider all surgeries a patient undergoes on the side of the injured knee affecting his/her mobility. Re-surgery following re-rupture will be considered as a failure.

If the proximal ACL rupture is not suitable for repair, the patient will undergo an ACL reconstruction (exploratory group). These patients will be followed according to this protocol except for the post-operative MRI measurements on week 52 and 104, and the post-operative isokinetic measurements on week 13, 26 and 52 as these measurements are study-specific and not standard of care.

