### Statistical analyses

#### Analysis of the primary outcome

To answer the research question comparing the three treatment arms the research question is split up in three separate questions:
*Is there a difference between DIS and IBLA (≤4 weeks)?*

Results from study 1 will be used in a linear regression model with IKDC at 6 months as outcome and treatment, and IKDC at baseline as predictors. This linear regression model will allow correction for possible confounders like age, gender and working category.
*Is there a difference between IBLA (5–12 weeks) and conventional ACL reconstruction?*

Results from study 2 will be used in a linear regression model with IKDC at 6 months as outcome and treatment, and IKDC at baseline as predictors. This linear regression model will allow correction for possible confounders like age, gender and working category.
*Is there a difference between DIS and conventional ACL reconstruction?*

Results from study 1 and study 2 will be compared using a linear regression model with IKDC at 6 months as outcome and treatment, and IKDC at baseline as predictors. As this is a non-randomized comparison this model will correct for possible confounders like age, gender and working category.

For the primary analysis all patients that didn’t have a repairable, proximal ACL rupture will be excluded from the analysis (exploratory group). Patients with a failure or re-surgery will be included in the primary analysis.

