#### Analysis of the secondary outcomes

To evaluate robustness of the results a sensitivity analysis of the primary outcome will be done using different analysis sets.Analysis set without failures: patients that have a failure within the 6 months of follow-up are excluded from this analysisAnalysis set without re-surgeries: patients that have a re-surgery within the 6 months of follow-up are excluded from this analysisIn case we are not able to show superiority between the arms, we will consider non-inferiority between the arms. To this end we will choose 10 IKDC points as non-inferiority margin (see Hoogeslag et al. [25]). Non-inferiority will be considered in the different analysis sets and only be concluded if they give similar findings. The analysis sets considered here are intention-to-treat, the analysis set without failures and the analysis set without re-surgeries.As the IKDC scores are measured at many different time points during the patient’s follow-up we can compare the evolution over time between the treatment arms using a linear mixed model. Also here we will consider the effect of failure and re-surgery through inclusion and exclusion of the results after failure.Linear regression will be performed on the changes from baseline to 24 months in the continuous outcomes like VAS pain, VAS satisfaction, Tegner score, Lysholm score, EQ-5D-5 L, Lachman test, single leg and triple leg hop test, triple crossover hop and drop jump test, isokinetic and proprioceptive measurement and knee function. The evolution over time of these continuous outcomes will be compared between the different treatments using a linear mixed model.A survival analysis with log-rank test will be used to compare the time to return to work and time to return to sports between the different treatment arms. The time from the surgery until the patient is mobile without crutches will be analysed in the same way.The number of physiotherapy/orthopaedic surgeon consults will be compared between the different treatment arms using linear regression.The morphology and signal intensity of the ACL will be assessed with MRI and compared between the different treatments using a Chi-square test at the different time points.

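### After a failed repair is replaced by a reconstruction, later MRIs of the rescue graft would enter the ACL-healing comparison as DIS or IBLA results

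*Protocol article*

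**What the plan says.** - **Rescue.** The paragraph after Fig. 5 that closes the Study intervention section states: "In case of failure/re-rupture of the repaired ACL (DIS/IBLA technique) a conventional ACL reconstruction can be performed". It also permits a failed reconstruction to be revised.
- **Follow-up.** Study procedures states: "When re-surgery is needed or a failure occurs, the patient is not excluded from the study and the follow-up will continue according to this protocol". Table 1 places MRI before surgery and at weeks 26, 52 and 104.
- **Endpoint.** Secondary endpoints lists: "ACL healing will be evaluated with MRI". Under Study procedures, an adapted 4-level Howell classification is used, and the reader grades whichever structure is in the knee, graft or repair.
- **Analysis.** Analysis of the secondary outcomes states: "The morphology and signal intensity of the ACL will be assessed with MRI and compared between the different treatments using a Chi-square test", at each time point. The abstract adds: "The statistical analysis will be based on the intention-to-treat principle".
- **Handling of failures.** For the primary outcome: "Patients with a failure or re-surgery will be included in the primary analysis". The sets without failures or re-surgeries are introduced by: "To evaluate robustness of the results a sensitivity analysis of the primary outcome will be done using different analysis sets". They cover events within 6 months and serve also for the non-inferiority check. Including and excluding results after failure is described for the IKDC mixed model. Nothing comparable is attached to the MRI comparison.

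**The concern.** For a patient-level outcome such as the IKDC score, keeping a rescued patient in the randomised arm answers a sensible question: how do patients fare when their treatment starts with this technique? MRI healing is a different kind of endpoint. It is a statement about one structure, the repaired ligament or the graft placed at the study operation. Once that structure has been replaced, a later image shows something else, and its grade carries no information on whether the original repair healed.

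The Discussion says that longitudinal MRI after repair is meant to inform on healing and potential failures. A rescue graft graded under the repair arm works against that purpose, and nothing in the planned table would mark the reading as coming from a different ligament.

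**Working it through.** **1. Trace one patient through the plan.** A patient is randomised to IBLA, the repair re-ruptures at month 8, and a reconstruction follows at month 9 (invented timing, for illustration).

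- Week 26: the MRI shows the repair. It is graded correctly under IBLA.
- Weeks 52 and 104: the patient is still on schedule, and the MRI shows a reconstruction graft. The grading scale accepts grafts. The Chi-square comparison is by treatment, and the analysis principle is intention-to-treat, so the grade is tabulated under IBLA.
- The failure sets do not reach this patient's MRI. They concern the primary outcome and events up to 6 months. The after-failure rule belongs to the IKDC mixed model.

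**2. The plan's own sample size, for reference.** Inputs from Sample size: difference 13, SD 13, alpha 0.025 (taken as two-sided), power 80%.

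- Normal approximation: n = 2 × (2.241 + 0.842)² × 13²/13² = 19.0, rounded up to 20 per arm.
- t-test: 20.3, rounded up to 21 per arm.
- Dropout of 10%: 21/0.9 = 23.3, rounded up to 24 per arm.

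The stated 21 and 24 reproduce, and this point does not affect them.

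**3. Expected number of patients affected.** Inputs from Background: 2 of 42 (4.8%) re-ruptures at 2 years with IBLA, and 96% stable healing with DIS, hence about 4% without it. Assumption: every failure is replaced before the MRI visit. Expected number = n × p. Chance of at least one = 1 − (1 − p)ⁿ.

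| Rate | n | Expected | Chance of at least one | Chance of two or more |
|---|---|---|---|---|
| 2/42 (IBLA) | 24 | 1.14 | 69% | 32% |
| 4% (DIS) | 24 | 0.96 | 62% | 25% |
| 2/42 applied to all three repair arms | 72 | 3.43 | 97% | 86% |

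The protocol's failure definition also includes instability, so the failure rate could be higher than the re-rupture rate. The article gives no figure for this. An assumed 10% to 20%, all replaced, would give 24 × 0.10 = 2.4 to 24 × 0.20 = 4.8 patients per repair arm. That is an upper range, because not every failure by instability leads to replacement.

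**4. Effect of one patient.** 1/24 = 4.2 percentage points on an arm's proportion in any MRI category.

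**5. Direction.** Background states that graft revascularisation takes 6–12 months and ingrowth into bone up to 2 years. A graft placed during follow-up may look mature or immature at week 104, so the sign of the distortion cannot be derived from the document.

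**The case against.** **Silence in a condensed article.** The rescue sentence is not itself wrong, and rules for data after re-surgery often sit in the SAP, which is not shown. The sentence on results after failure does not forbid the same handling elsewhere. This stands in part: the SAP may already settle the matter. But the article does fix the MRI analysis, and in the same section it sets out post-failure handling for the IKDC alone. Followed as written, it yields a wrong measurement.

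**Failures are not lost.** A reader might infer that the plan hides repair failure. The documents do not support that. The number of non-failures is a secondary endpoint, re-surgery after re-rupture counts as a failure, and comparing failures is a stated objective. Only the MRI table is affected.

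**Lachman.** A reader might extend the point to the 24-month Lachman comparison. The article lists Lachman under mechanical function of the knee, beside the hop and isokinetic tests. Analysing knee function as randomised, rescue included, is defensible there, and Lachman already forms part of the failure definition. The same holds for the IKDC, which has its own failure analyses.

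**Asymmetric rescue.** A reader might see a systematic pull of the repair arms towards reconstruction. In study 1 both arms share the same rescue and there is no reconstruction arm. In study 2 a failed reconstruction may also be revised, so a second graft can be read under that arm too. A general bias in favour of repair does not follow.

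**Conclusion.** The point holds for the MRI comparison alone. Under the plan as written, the image of a replacement graft is graded as healing of a ligament that has been removed, in whichever arm this happens.

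The likely size is small: about 1 of 24 patients per repair arm at the article's own rates, or 4.2 points on a category proportion. This assumes that those rates apply here and that every failure is replaced before the visit. The direction is open. The primary analysis, the sample size, the failure endpoint and the functional outcomes are unaffected. The change is worth making because the misattribution is certain for each patient to whom it applies, and the remedy costs almost nothing.

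**What to change.** In Analysis of the secondary outcomes, add to the MRI item, for all three arms: a patient whose repaired ligament or graft was replaced before the visit is placed in a failed/replaced (not healed) category from that visit on, and the reading of the new graft is shown only as a supplementary line.

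- Failures without replacement keep their actual MRI grade. A failure by instability can leave a ligament that MRI can still grade.
- IKDC, Lachman and the other functional outcomes stay as randomised. For Lachman, a sensitivity analysis excluding results after re-surgery, in line with what is planned for the IKDC mixed model, is optional.

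No new data appear necessary, since the 6-month analysis sets and the IKDC rule already require the dates of failure and re-surgery. The cost is one sentence and one extra, sparse category in the Chi-square table. If the SAP already contains such a rule, a cross-reference is enough. Clinical management does not change.
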